### Research Goals

The trial will compare the efficacy of topiramate with placebo in the treatment of PTSD, and will study its tolerability through the drop out rate in each group. The primary hypothesis is that topiramate will be superior to placebo in the treatment of PTSD. Secondary research goals includes studying the efficacy of topiramate in social adjustment, functioning and quality of life. Additionally, evaluating treatment adhesion, and studying the efficacy of topiramate in depressive symptoms.

## Materials and methods

### Subjects

All elegible patients admitted at the outpatient clinic from the violence program of Federal University of São Paulo Hospital (UNIFESP) who read and signed a consent inform approved by the UNIFESP Institutional Review Board (IRB) will enter the study. A pre-request to be admitted at this program is having passed through a stressor event which imposed a risk on subjects' physical and/or psychological integrity (DSM-IV criterion A for PTSD diagnostic). Patients looked for an appointment at the program spontaneously, or through health worker recommendation or were called by phone or by mail from a list of subjects which had a PTSD diagnostic after a CIDI submission by trained raters on the Sao Paulo epidemiological catchment area study. This was an epidemiological survey of a random sample of 3000 participants living in the city of Sao Paulo to assess the relationship between exposure to violence and the prevalence of PTSD and common mental disorders.

All patients will be administered the Structured Clinical Interviews for DSM-IV Axis I and Axis II (SCID-I and SCID-II, respectively) by a trained psychiatrist [31,32]. Patients will be eligible if they meet the inclusion criteria: 1) DSM-IV criteria for a diagnosis of PTSD [1], 2) both gender, aged between 18 to 60 years of age. 3) Women of childbearing potential have to be practicing reliable contraception and cannot be pregnant or breast-feeding during the course of the study. The exclusion criteria will be: 1) lifetime history of bipolar, psychotic, borderline personality disorder; substance dependence or abuse (excluding nicotine and caffeine) in the previous 6 months; 2) serious or unstable concurrent illness; history of nephrolithiasis, 3) use of psychotropic medications for the previous 2 weeks (6 weeks for fluoxetine); 4) body mass index below 20; 5) current suicidal ideation or psychotic symptoms will be excluded from the study.

### Measures

• *The Structured Clinical Interview for DSM-IV-Axis I and II *(SCID-I and II) [31,32]: is a semi-structured interview that allows for the diagnosis of Axis I and II disorders, respectively, according to DSM-IV criteria [1].

• *The Clinician-Administered PTSD Scale *(CAPS) [33]: is a structured interview developed to diagnose PTSD and rate its severity. It is comprised of 30-items to assess PTSD-related symptom frequency and severity. Scores range from 0 to 136, with scores classified as follows: subclinical, from 0 to 19; mild, from 20 to 39; moderate, from 40 to 59; severe, from 60 to 79; extreme, 80 and above.

• *The Beck Depression Inventory *(BDI) [34]: is a 21-item self-report inventory designed to measure the severity of depression. Scores range from 0 to 63, with depression classified as minimal when scores range from 0 to 11, mild from 12 to 19, moderate from 20 to 35, and severe from 36 to 63.

• *MOS 36-Item Short-Form Health Survey *(SF-36) [35]: is a scale to measure mental and physical health concepts. It is a 36-item self-report instrument. The SF- 36 measures social functioning correlated to clinical conditions. As higher is the score, better is the quality of life. The instrument gave a global score, as specific areas scores: functional capacity, physical aspects, pain, general health condition, vitality, social aspects and emotional aspects, and mental health.

• *Social Adjustment Scale *(SAS) [37]: is a 54-item scale, ranging from 1 to 5 from normal to severely misadjusted. Used to evaluate social adjustment, normal score is around 1.56 (+/- .36).

• *Global Assessment of Functioning (GAF) Scale *[38]: is a single-item rating scale for evaluation the overall patient functioning during a specified period on a continuum from psychological or psychiatric sickness to health. The scale value ranges from 1 (hypothetically sickest person) to 100 (hypothetically healthiest person), divided into 10 equal intervals. A modified version of the Global Assessment Scale (GAS) was included in DSM-III as the Global Assessment of Functioning (GAF) Scale.

• *The Clinical Global Impression – Severity scale (CGI-S) *[37]: is a 7-point scale that requires the clinician to rate the severity of the patient's illness at the time of assessment, relative to the clinician's past experience with patients who have the same diagnosis. Considering total clinical experience, a patient is assessed on severity of mental illness at the time of rating 1 = normal, not at all ill; 2, borderline mentally ill; 3, mildly ill; 4, moderately ill; 5, markedly ill; 6, severely ill; or 7, extremely ill.

• *The Clinical Global Impression – Improvement scale (CGI-I) *[38]: is a 7 point scale that requires the clinician to assess how much the patient's illness has improved or worsened relative to a baseline state at the beginning of the intervention, and rated as: 1, very much improved; 2, much improved; 3, minimally improved; 4, no change; 5, minimally worse; 6, much worse; or 7, very much worse.

### Study design

This is a 12-week randomized, double-blind, placebo-controlled clinical trial that will be conducted at the Federal University of São Paulo Hospital (UNIFESP). The study was approved by UNIFESP Institutional Review Board (IRB), and will follow the Helsinky Declaration, and the local ethical laws. Ethical Committee: 196/96

#### Screening Phase

After the SCID-I and II administration, eligible patients will undergo a brief physical examination with height, weight, heart rate and systemic blood pressure measured and a clinical evaluation including electrocardiogram (EKG) and laboratory blood test for complete blood count, fasting glycemia, sodium, potassium, urea, creatinine, T3, T4, and TSH. Women will have a pregnancy test done, to assure they are not pregnant. The psychiatrist who administered the SCID, will also evaluate patients clinical conditions and functionality through CGI-S and GAF. The Clinician-Administered Posttraumatic Stress Scale (CAPS)[33] will be administered to the patients by trained raters, patients also will completed the Beck depression inventory (BDI) [34], the medical outcomes self-report (SF-36)[35] and the social adjustment scale (SAS) [36].

#### Wash-out phase

Patients will receive placebo pills and will be re-evaluated by the same psychiatrist one week after. Those having a significant improvement of the symptoms (a CGI-I score less than 3) will be excluded (avoiding premature placebo effects).

#### Active treatment phase

Those patients without improvement during the placebo trial, and do not show any laboratory and clinical condition exclusion criteria will be randomly assigned to receive either placebo or topiramate, in a 1:1 ratio using computer- generated code. The active and placebo pills will be identical. All research and clinical staff will be blinded to the randomized assignments.

Study medication will start at 25 mg/day once daily, at night, and will be increased 25 mg weekly, as tolerated, until complete or nearly complete efficacy is achieved or until 200 mg/day is reached. No other psychotropic medications will be allowed during the study, except for zolpidem (10 mg/day), if needed, for insomnia.

Study follow-up visits will be conducted at baseline, and weeks 1, 2, 3, 4, 6, 8, and 12.

Symptoms and side effects will be assessed, as well as measurement of systemic blood pressure and pulse rate in each visit by the investigator, who is blind to medication assignment. Compliance will be assessed by counting the amount of pills left in the bottle of medicine in each visit.

Treatment will be continued for 12 weeks (active treatment phase); then drug administration will be withdrawn gradually during 2 weeks with reductions of 25/50 mg every three days, according to the final dosage reached.

Patients will be assessed until completing 6 months during a follow-up period. If a patient showed a symptomatology worsening during the active treatment phase (12 weeks) when receiving active drug treatment, characterized by a one-point decrease at CGI -I or present serious adverse effects related to medication, he/she will be excluded from the study.

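### The withdrawal rule states the CGI-I direction backwards: the one-point fall it calls worsening is always an improvement

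*Protocol article*

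**What the plan says.** The rule is one sentence in the Active treatment phase section of the Protocol article. It names the condition and its threshold together, "symptomatology worsening during the active treatment phase (12 weeks) when receiving active drug treatment, characterized by a one-point decrease at CGI -I", and then adds a second trigger and the consequence: "characterized by a one-point decrease at CGI -I or present serious adverse effects related to medication, he/she will be excluded from the study".

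The scale is defined under Measures. CGI-I has seven points: "1, very much improved; 2, much improved; 3, minimally improved; 4, no change; 5, minimally worse; 6, much worse; or 7, very much worse". The same entry says that the rating is made against the patient's state at the start of the intervention.

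The Wash-out phase section uses CGI-I once more: "Those having a significant improvement of the symptoms (a CGI-I score less than 3) will be excluded".

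Removal from the study bears on two stated results. Aims of the Study measures tolerability by the dropout rate in each group, and Statistical Analysis compares the proportions completing 12 weeks by a chi-square test. Statistical Analysis also fills missing week-12 efficacy data, including the primary CAPS endpoint, by last observation carried forward.

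**The concern.** The condition and its threshold point in opposite directions. The sentence names worsening but measures it by a falling score, on a scale where falling scores mean improvement. Whoever applies the rule must choose between the word and the number.

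Three things depend on that choice:

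- **Patient protection.** If the number is followed, a deteriorating patient does not meet the rule and stays on treatment. The serious-adverse-effects trigger does not cover worsening of PTSD symptoms.
- **Tolerability.** A patient removed under the rule does not complete the 12 weeks and so enters the dropout and completion comparisons.
- **Primary endpoint.** A removed patient with no week-12 CAPS score contributes the last one available, so who is removed, and when, affects which value is analysed.

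**Working it through.** There is no planned figure to reproduce. The check is one of scale direction.

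**Inputs**

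- Threshold: a one-point decrease on CGI-I (Active treatment phase).
- Condition it is meant to capture: symptom worsening (same sentence).
- Scale: 1 best, 4 no change, 7 worst, rated against baseline (Measures).
- Second use of the scale: below 3 counts as significant improvement (Wash-out phase).

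**Step 1. List every one-point decrease.** A 7-point scale allows 7 − 1 = 6 of them.

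| From | To | Direction of the step |
|---|---|---|
| 7 | 6 | improvement |
| 6 | 5 | improvement |
| 5 | 4 | improvement |
| 4 | 3 | improvement |
| 3 | 2 | improvement |
| 2 | 1 | improvement |

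Six of six are improvements and none is a worsening. The steps from 7 to 6 and from 6 to 5 leave the patient rated worse than at baseline, but each is better than the rating before it. Neither step can therefore mark the onset of worsening.

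**Step 2. Apply the rule to a patient rated 4 (no change).**

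- The patient moves to 5, minimally worse. The score has risen, so the written threshold is not met.
- The patient moves to 3, minimally improved. The score has fallen by one, so the written threshold is met.

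**Step 3. See whether another part of the article reconciles this.**

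- The Wash-out phase reads low CGI-I scores as improvement. It agrees with Measures and disagrees with the withdrawal rule.
- If CGI-S was meant, the direction is still wrong. Measures runs that scale from 1 for normal up to "4, moderately ill; 5, markedly ill; 6, severely ill; or 7, extremely ill", so a decrease there is an improvement too.
- No other section gives a reversed scale or a second definition of worsening.

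**Step 4. Correct the direction.** CGI-I is rated against baseline, so worse than baseline means 4 + 1 = 5 or higher. No design figure changes.

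**The case against.** The strongest reply is that this is a slip of language which no clinician would follow. The sentence names worsening before it gives the number. The Wash-out phase shows that the authors know which way the scale runs. The article's English is unidiomatic in places, so decrease may simply have been meant as clinical decline. All of this is fair, and it limits how serious the point is. It does not make the threshold correct: the score change is the only operational definition of worsening offered, and it is reversed.

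A reader might infer more than the article supports, in three ways:

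- **That improving patients will in fact be withdrawn and the efficacy result biased.** This needs the literal reading to be followed in practice. The stated intent makes that unlikely, and nothing in the article shows it.
- **That several raters will apply the rule in different directions.** The article describes one centre, a wash-out re-evaluation by the same psychiatrist, and visit assessments by one investigator: "Symptoms and side effects will be assessed, as well as measurement of systemic blood pressure and pulse rate in each visit by the investigator". The trained raters it mentions administer CAPS. Disagreement between raters over this rule is not documented.
- **That the visit schedule gives the size of the problem.** The article lists the visits ("Study follow-up visits will be conducted at baseline, and weeks 1, 2, 3, 4, 6, 8, and 12") but does not say that CGI-I is rated at each one. A count of visits would measure opportunity at most, not harm.

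**Conclusion.** The concern holds as an error of direction in a decision rule. On the article's own scale, none of the six possible one-point decreases is a worsening, and nothing elsewhere in the article corrects the sentence. The conclusion rests only on the anchors under Measures and needs no outside source.

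The practical effect is probably small, because the intent can be read from the sentence. It cannot be put as a number of patients: the article gives no expected rate of worsening, no CGI-I rating schedule and no interim CAPS schedule. The point still merits correction, because the rule removes patients, removal feeds the dropout comparison and the carried-forward primary endpoint, and the repair costs almost nothing.

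**What to change.** Replace the score condition in the withdrawal sentence with: *a CGI-I score of 5 or more (at least one point worse than 4, no change, relative to baseline)*.

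A fixed score is preferable to simply changing the word to increase. A one-point increase could be read as a change since the previous visit. It would then remove a patient who went from 2 to 3 and is still better than at baseline. A fixed score follows the definition of CGI-I as a rating against baseline and matches the form of the wash-out criterion. If worsening since the previous visit was intended, the sponsor should say so and state that reference point.

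The sentence also refers to patients on active drug, although staff are blinded. If it is to be worded for blinded staff, replace that phrase with *while receiving study medication*. Do not add a phrase about either arm beside the existing one, because the two would conflict.

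Leave the serious-adverse-effects trigger as it is. The cost is a wording correction to one clause, or two phrases if the blinding wording is also changed. It needs no new visit, assessment or change to the analysis.

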### Sample Size

The number of subjects calculated for the trial is 72, being 36 on each cell. The sample size was calculated considering a 5% probability of type I error (significance level), and 20% for type II error (power test of 80%), on a bi-caudal test. To the calculation we use an average of 60% for response from PTSD for active drugs, based on published literature, and 30% of placebo response.

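### With 36 per arm, the power to detect 60% versus 30% response is about 73% on the planned chi-square test, not the stated 80%

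*Protocol article*

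**What the plan says.** The Sample Size section of the protocol article gives a complete set of inputs and a result:

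- Result: "The number of subjects calculated for the trial is 72, being 36 on each cell".
- Significance level: "considering a 5% probability of type I error (significance level".
- Power and sidedness: "20% for type II error (power test of 80%), on a bi-caudal test".
- Effect: "we use an average of 60% for response from PTSD for active drugs, based on published literature, and 30% of placebo response".

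The section names no formula. The Active treatment phase section sets 1:1 allocation. The Statistical Analysis section compares response (a 20% improvement on the CAPS) between arms with a chi-square test. The same section makes change in CAPS total score at 12 weeks the primary efficacy endpoint and analyses the scales by ANOVA. It mentions Fisher's test for the CAPS severity categories when cells are sparse.

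**The concern.** Significance level, sidedness, power, both response rates and allocation are all stated, so the number per arm can be recalculated without guessing. The result should match 36 to within rounding or the choice of formula, and it does not.

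This calculation is the only quantitative justification given for the trial's size. If response does not differ significantly between arms, a reader will assume that a true 60% versus 30% difference would be missed one time in five. On the planned test it would be missed more than one time in four.

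**Working it through.** **Inputs.** p1 = 0.60, p2 = 0.30, difference 0.30, two-sided 5% (z = 1.960), 80% power (z = 0.8416): all from Sample Size. Allocation 1:1: from Active treatment phase. Mean proportion 0.45. Variance terms: 2 × 0.45 × 0.55 = 0.495 (pooled); 0.60 × 0.40 + 0.30 × 0.70 = 0.45 (unpooled).

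**Attempt to reproduce 36 per arm (two-sided)**

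- Unpooled: n = 0.45 × (1.960 + 0.8416)² / 0.30² = 0.45 × 7.849 / 0.09 = 39.2, so 40.
- Pooled (the usual chi-square formula): n = (1.960 × √0.495 + 0.8416 × √0.45)² / 0.09 = (1.379 + 0.565)² / 0.09 = 41.97, so 42.
- Arcsine: 41.8, so 42.
- Simple pooled, with 0.495 used for both terms: 0.495 × 7.849 / 0.09 = 43.2, so 44.
- Continuity-corrected: n = (41.97 / 4) × (1 + √(1 + 4 / (41.97 × 0.30)))² = 48.4, so 49.

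None gives 36. The smallest total is 80 and the pooled formula gives 84, against the stated 72.

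**Power at 36 per arm (two-sided 5%)**

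- Pooled formula: z = (0.30 × √36 − 1.379) / √0.45 = (1.800 − 1.379) / 0.6708 = 0.628, so power is 73.5%.
- Unpooled: z = 0.30 / √(0.45 / 36) − 1.960 = 2.683 − 1.960 = 0.723, so power is 76.5%.
- Arcsine: 73.9%.
- Uncorrected chi-square, summing the binomial probabilities of all 37 × 37 possible outcomes that reach p ≤ 0.05: 72.7%.

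The most favourable variant still falls short of 80%. On the planned test the type II error is 100 − 72.7 = 27.3% (exact) or 100 − 73.5 = 26.5% (formula), about 27%.

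**What 36 per arm can detect with 80% power, placebo held at 30%**

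| Active response | Pooled formula | Exact chi-square |
|---|---|---|
| 62% | 79.0% | 78.1% |
| 62.4% | 80.0% | 79.1% |
| 63% | 81.5% | 80.6% |

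Both methods pass 80% at about 63% versus 30%.

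**The case against.** **The primary endpoint is not response.** This is correct and it limits the point. A reader might infer that the trial has only 73% power for its main question. The document does not support that, because the primary comparison is of a continuous score. As an illustration only, assume normal scores with equal variance and one response cut-off. Then 60% versus 30% corresponds to a standardised difference of 0.253 + 0.524 = 0.78, and a two-sided t-test with 36 per arm has about 90% power. At 80% power the detectable difference is 0.67. These assumptions are not in the document, so neither 73% nor 90% can be stated as the power of the primary test.

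**Fisher's test gives a worse figure.** By exact enumeration its power is 63.6%, and a reader might quote that. But the article plans chi-square for response and mentions Fisher's test for sparse severity categories. Expected counts in the response table are 36 × 0.60 = 21.6 and 14.4, and 36 × 0.30 = 10.8 and 25.2. The chance of any cell below five is under 1%. The Fisher figure does not describe the planned comparison.

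**The calculation may have been one-sided.** One-sided 5% formulas give 31 (unpooled), 33 (pooled or arcsine), 35 (simple pooled, 34.0 rounded up) and 40 (continuity-corrected). One-sided Fisher has 79.5% power at 36 per arm. A one-sided origin is thus possible, but it is conjecture and it contradicts "on a bi-caudal test". The section would still be wrong as written.

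**Dropout would make it worse.** The Background cites a topiramate trial in which 55% and 25% did not complete, so a reader might add a missing dropout allowance to the charge. That trial was a seven-week augmentation study in male veterans. The present plan keeps dropouts in the analysis by carrying the last observation forward, and a condensed article may leave the allowance to the full protocol. The arithmetic fails with no dropout at all, so this is not part of the point.

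**Conclusion.** The stated 80% power does not follow from the stated inputs. On the planned chi-square test, 36 per arm gives about 73% power for 60% versus 30%, a shortfall of about 7 percentage points. Equivalently, 80% power by the pooled formula needs 42 − 36 = 6 more patients per arm, or 12 in total.

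This rests on the article's own response rates, 1:1 allocation, a two-sided 5% level, the uncorrected chi-square test and all 72 patients analysed. It concerns only the response comparison. It does not show that the primary CAPS analysis is underpowered, and it does not show how 36 was obtained.

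**What to change.** Keep 72 patients and replace the power statement in Sample Size with wording such as:

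> With 36 patients per arm, the trial has about 73% power (two-sided 5%, chi-square test) to detect response rates of 60% versus 30%; 80% power is reached for about 63% versus 30%. This calculation refers to the response outcome and not to the primary endpoint, the change in CAPS total score.

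This changes wording only: no patient, procedure or analysis is affected. The cost is a slightly less favourable stated power. If 80% power for 60% versus 30% is to be kept, the stated total must instead rise to 84 (2 × 42, pooled formula).

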Clinical studies with topiramate suggest that it is effective as monotherapy or adjunctive therapy in PTSD. Two open-label studies demonstrated topiramate to be effective and to have a rapid onset of action. Berlant and van Kammen [27] have reported that topiramate decreased nightmares in 79% and flashbacks in 86% of civilian patients with chronic PTSD with improvement of nightmares in 50% and of intrusions in 54% of patients with these symptoms. A partial response was reported for 95% of patients at a dosage of 75 mg/day or less and in 91% of full responders at a dosage of 100 mg/day or less. The nonhallucinatory subgroup achieved a higher response rate (89%). In a prospective open-label study, Berlant [28] treated thirty three civilians with chronic PTSD, with topiramate as monotherapy or augmentation therapy. The PTSD Checklist-Civilian Version (PCL-C) total symptoms declined by 49% at 4th week, with similar subscale reductions for reexperiencing, avoidance/numbing, and hyperarousal symptoms. Topiramate suppressed nightmares in 79% and decreased symptoms of intrusions in 94% in those patients with these symptoms. There is only one double-blind, placebo- controlled study of topiramate as a monotherapy in PTSD. Tucker [29] conducted a 12-week, double-blind, placebo-controlled evaluation of topiramate as a monotherapy in thirty eight civilian PTSD patients. Patients in the topiramate group exhibited significant reductions in reexperiencing symptoms (CAPS cluster B: topiramate = 74.9%; placebo = 50.2%; p = .038) and reductions approaching statistical significance, based on a nominal p value, were noted in mean total Clinical Global Impressions-Improvement Scale scores (topiramate = 1.9 ± 1.2; placebo = 2.6 ± 1.1; p = .055). Although there was a reduction in total Clinician-Administered PTSD Scale (CAPS) score from baseline (topiramate = -52.7; placebo = -42.0), the difference was not statistically significant (p = .232). But not all studies found positive results, Lindley [30] in a double-blind, placebo-controlled study using topiramate as an augmentation therapy in forty male veterans with PTSD did not find significant treatment effects versus placebo. However, there was a high dropout rate from the study with 11 (55%) topiramate and 5 (25%) placebo subjects not completing the seven week treatment, with 40% of topiramate and 10% of placebo dropping because of adverse effects. Patients in the topiramate group that completed the study, had a significant improvement in the reexperiencing subscale of the CAPS suggesting efficacy for the patients that continued the medication.

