Efficacy analyses will be performed in the intent-to-treat population of patients who received at least one dose of topiramate. The primary efficacy endpoint will be the change in PTSD Scale- CAPS total score from baseline to the final visit at 12 weeks, which will be compared between treatment groups. Missing efficacy data at 12 weeks will be imputed with the last observation carried forward. The secondary outcomes between groups will be comparing the Clinical Global Impressions (CGI), the Beck Depression Inventory (BDI), the Global Assessment of Function (GAF), and the PANAS scales. Other secondary analyses will include an evaluation after 24-weeks (12-week after last patient visit with drug) data with endpoint analyses between the treatment groups covarying for baseline scores. On all secondary outcomes, the Bonferroni correction will be applied for testing multiple variables. Response will be defined as a 20% improvement in the baseline CAPS total or positive symptom scores at 12 weeks and will be compared between treatment groups using a chi-square test. Proportions of patients completing the 12-week double-blind study will be compared between treatment groups using a chi-square test. Adverse events reported by 10% of patients in each treatment group will be compared using a chi-square test. Laboratory values, vital signs and physical examinations are going to be compared from baseline and in reference to normal ranges, and reported as normal or abnormal. Changes in body weight (lb), body mass index (BMI; kg/m2) at last visit in the 12-week dataset will be compared as mean changes between treatment groups using t-tests.

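### 36 per arm gives about 73% power, not 80%, for 60% vs 30% response with complete data, so the 72 patients hold no allowance for the dropout the protocol expects

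*Protocol article*

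**What the plan says.** The Sample Size section gives the whole calculation in a few lines: "The number of subjects calculated for the trial is 72, being 36 on each cell", "considering a 5% probability of type I error (significance level"), "20% for type II error (power test of 80"%), "on a bi-caudal test". For the rates, "we use an average of 60% for response from PTSD for active drugs, based on published literature", against 30% on placebo. Dropout is not mentioned.

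Elsewhere the article treats dropout as expected:

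- The Background reports a controlled topiramate augmentation trial with "11 (55%) topiramate and 5 (25%) placebo subjects not completing the seven week treatment".
- Aims of the Study makes the dropout rate in each group the measure of tolerability, and Statistical Analysis compares completion between groups by chi-square.
- Under Active treatment phase, a patient who worsens on active drug or has serious drug-related adverse effects is removed: "he/she will be excluded from the study".

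Statistical Analysis sets an intention-to-treat analysis in which "Missing efficacy data at 12 weeks will be imputed with the last observation carried forward". Response is a 20% improvement in CAPS, compared by chi-square. The primary endpoint is the change in CAPS total score.

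**The concern.** A sample size that is silent on dropout, in a protocol that plans to measure dropout, raises two questions. Does the stated power follow from the stated inputs? If so, does 72 leave any margin for patients who leave early?

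The answer affects how the result is read. A non-significant responder comparison would be judged against a claimed 80% chance of detecting a doubling of response, from 30% to 60%. If the real figure is lower, such a result is weaker evidence against topiramate than readers would think.

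**Working it through.** **Inputs (Sample Size section).** Two-sided alpha 0.05 (z = 1.960), power 0.80 (z = 0.842), p1 = 0.60, p2 = 0.30, n = 36 per arm. Allocation is 1:1 (Active treatment phase).

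**Step 1: the plan's own figure.** With mean rate 0.45, the pooled two-proportion formula is

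n = [1.960 × √(2 × 0.45 × 0.55) + 0.842 × √(0.60 × 0.40 + 0.30 × 0.70)]² / (0.30)²

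= [1.960 × 0.7036 + 0.842 × 0.6708]² / 0.09 ≈ 41.97, so 42 per arm, 84 in total.

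Other two-sided versions give 40 (unpooled), 42 (arcsine), 44 (pooled variance in both terms) and 49 (continuity-corrected). None gives 36. One-sided versions come close: 33 per arm, which about 8% dropout would raise to 36 (33/36 = 0.917), or 35 per arm with pooled variance in both terms. Both contradict the stated two-sided test.

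**Step 2: power at 36 per arm, complete data.**

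z = [0.30 × √36 − 1.960 × 0.7036] / 0.6708 ≈ 0.628, so power is 73.5%.

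Exact enumeration of the two binomials with the uncorrected chi-square test gives 72.7%. The unpooled approximation gives 76.5% and Fisher's exact test 63.6%. None reaches 80%.

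**Step 3: dropout.** Under last observation carried forward all 36 per arm stay in the denominator, so the number analysed does not shrink. The observed response rates may fall instead. If a share d drops out and dropouts respond at a fraction f of the completer rate, the rate entering the test is p × (1 − d) + f × p × d. The article gives no dropout rate for this trial, so the values of d are assumptions. So is the reading of 60% and 30% as completer rates. Exact chi-square power at 36 per arm:

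| Dropout, topiramate / placebo | Rates if f = 0 | Power | Rates if f = 0.5 | Power |
|---|---|---|---|---|
| 0% / 0% | 0.60 vs 0.30 | 73% | 0.60 vs 0.30 | 73% |
| 10% / 10% | 0.54 vs 0.27 | 65% | 0.57 vs 0.285 | 69% |
| 20% / 20% | 0.48 vs 0.24 | 58% | 0.54 vs 0.27 | 65% |
| 25% / 15% | 0.45 vs 0.255 | 42% | 0.525 vs 0.2775 | 58% |

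The column f = 0 holds if every dropout is carried at baseline, since an unchanged CAPS cannot show a 20% improvement. If 60% and 30% already count dropouts as failures, the first row applies whatever the dropout.

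**Step 4: is this only a matter of starting too small?** No. At 42 per arm exact power is 82.8% with complete data, and 75% and 65% at 10% and 20% dropout with f = 0. The dropout question is separate from the shortfall in Step 1.

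**The case against.** The strongest reply is that a journal article may leave the assumed dropout rate to the full protocol, and that any loss from dropout rests on assumptions the article does not settle. Much of this stands. The missing rate alone would not be a finding. The article does not say whether 60% and 30% are completer or intention-to-treat rates. The pooled response rates in the Background (59.1% and 38.5%) come without a statement of how dropouts were counted. Nor is it settled that every dropout is carried at baseline. The analysis compares two CAPS measurements, but symptoms are assessed at every visit, and nothing rules out a CAPS at interim visits or on withdrawal. None of this rescues the 80%, which fails with complete data.

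Three stronger readings are tempting, and the article does not support them:

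- **That the 80% holds as long as nobody drops out.** Step 2 shows that it does not.
- **That 55% versus 25% should be the planning rate.** With f = 0 this gives 0.27 versus 0.225 and about 7% power. But those rates come from a seven-week augmentation trial in forty male veterans, while this is a 12-week trial with no other psychotropic drug except zolpidem. The Background gives no dropout for the closer study, a 12-week monotherapy trial in 38 civilians. The 55% and 25% are a warning only.
- **That the primary test has the power tabulated here.** The primary endpoint is a continuous change in CAPS, with no target difference or standard deviation given. Its power cannot be computed from the article.

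**Conclusion.** The point holds in this form. The stated 80% is wrong for the stated inputs: the power of the responder comparison is about 73% with complete data, and 72 is 12 patients short of the 84 those inputs require. Under the stated two-sided test, 72 therefore contains no allowance for dropout, although the article expects dropout.

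The further loss is conditional. It is nil if the two rates already count dropouts as failures. If they are completer rates, equal dropout of 10% to 20% leaves between 58% and 69%, depending on how dropouts respond. Dropout of 25% versus 15% leaves between 42% and 58%. The shortfall to 73% needs no assumption beyond the article's own inputs; everything below it rests on assumed dropout.

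**What to change.** In the Sample Size section:

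1. Replace the 80% with about 73%, described as the power of the responder comparison at 36 per arm with complete week-12 data. Do not explain the 80% as having assumed complete data, because that would be untrue.
2. Say whether 60% and 30% already count dropouts as failures.
3. If they do not, state an assumed dropout range per arm and the resulting power, using the table under the working: about 65% to 69% at 10% in both arms, 58% to 65% at 20%, and 42% to 58% at 25% versus 15%. Do not use 55% versus 25% as the planning rate.
4. Note that these figures do not apply to the primary CAPS change.

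Also reconcile the removal wording under Active treatment phase with Statistical Analysis, so that it is clear whether removed patients stay in the carried-forward analysis.

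The cost is a few sentences and a recalculated figure. No extra patients are needed. The only downside is a less favourable stated power.
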